## Abstract

**Background:**

High gestational weight gain is a major public health concern as it independently predicts adverse maternal and infant outcomes. Past interventions have had only limited success in effectively managing pregnancy weight gain, especially among women with overweight and obesity. Well-designed interventions are needed that take an individualized approach and target unique barriers to promote healthy weight gain.

**Objective:**

The primary aim of the study is to describe the study protocol for Healthy Mom Zone, an individually tailored, adaptive intervention for managing weight in pregnant women with overweight and obesity.

**Methods:**

The Healthy Mom Zone Intervention, based on theories of planned behavior and self-regulation and a model of energy balance, includes components (eg, education, self-monitoring, physical activity/healthy eating behaviors) that are adapted over the intervention (ie, increase in intensity) to better regulate weight gain. Decision rules inform when to adapt the intervention. In this randomized controlled trial, women are randomized to the intervention or standard care control group. The intervention is delivered from approximately 8-36 weeks gestation and includes step-ups in dosages (ie, Step-up 1 = education + physical activity + healthy eating active learning [cooking/recipes]; Step-up 2 = Step-up 1 + portion size, physical activity; Step-up 3 = Step-up 1 + 2 + grocery store feedback, physical activity); 5 maximum adaptations. Study measures are obtained at pre- and postintervention as well as daily (eg, weight), weekly (eg, energy intake/expenditure), and monthly (eg, psychological) over the study period. Analyses will include linear mixed-effects models, generalized estimating equations, and dynamical modeling to understand between-group and within-individual effects of the intervention on weight gain.

**Results:**

Recruitment of 31 pregnant women with overweight and obesity has occurred from January 2016 through July 2017. Baseline data have been collected for all participants. To date, 24 participants have completed the intervention and postintervention follow-up assessments, 3 are currently in progress, 1 dropped out, and 3 women had early miscarriages and are no longer active in the study. Of the 24 participants, 13 women have completed the intervention to date, of which 1 (8%, 1/13) received only the baseline intervention, 3 (23%, 3/13) received baseline + step-up 1, 6 (46%, 6/13) received baseline + step-up 1 + step-up 2, and 3 (23%, 3/13) received baseline + step-up 1 + step-up 2 +step-up 3. Data analysis is still ongoing through spring 2018.

**Conclusions:**

This is one of the first intervention studies to use an individually tailored, adaptive design to manage weight gain in pregnancy. Results from this study will be useful in designing a larger randomized trial to examine efficacy of this intervention and developing strategies for clinical application.

**Registered Report Identifier:**

RR1-10.2196/9220

## Introduction

### Background

Maternal weight gain in pregnancy is necessary for healthy fetal development [1]. The Institute of Medicine [1] recommends that appropriate weight gain for normal weight women is 25-35 pounds, whereas weight gain for overweight (15-25 pounds) and obese (11-20 pounds) women is less; any weight above these upper guidelines is considered excessive or high. High gestational weight gain (GWG) is strongly related to and independently predicts adverse pregnancy outcomes (eg, preterm delivery, gestational diabetes, and pre-eclampsia), greater adiposity, postpartum weight retention, and long-term obesity and cardiovascular disease [1,2]. Maternal obesity and high GWG also elevate infant risks such as macrosomia and early onset of obesity and diabetes [1]. As GWG is a modifiable factor that can be targeted to reduce adverse risks, managing GWG is critical for the mother, and can influence the etiology of obesity for offspring at a crucial time in the life cycle. However, over 50% of women enter pregnancy as already overweight (body mass index, BMI, 25-29.9 kg/m^2^) or obese (BMI ≥30 kg/m^2^) [3], and nearly 60% of women with overweight/obesity gain more weight in pregnancy than that recommended by the Institute of Medicine [1], which suggests they have particular challenges with managing their weight.

Past randomized intervention trials have shown that behavioral interventions can effectively manage weight in pregnant women [4-7] when they “mirror” effective programs in nonpregnant women such as using calorie goals, frequent contact and weight and dietary intake monitoring, and promoting healthy eating and exercise behaviors [8-10]. However, the effectiveness of these interventions has mainly been demonstrated in normal weight women. The results of studies including women with overweight and obesity are mixed. Several studies found little to no effect on GWG [5,6,11-13], whereas other interventions observed some effects [14,15] but were based on older guidelines [16] that were less restrictive than the current guidelines [1]. One study using current guidelines found a significant reduction in GWG (23 pounds) among women with obesity participating in a lifestyle intervention group compared with the 30 pound gain in the control group [17]. Both groups, however, exceeded the Institute of Medicine GWG guidelines [1]. In short, women with overweight and obesity have unique challenges with managing weight that may likely require a more intensive and tailored approach than what is traditionally delivered in usual prenatal care or has been tested in past interventions.

One strategy that has been used to facilitate behavior change in other areas (eg, mental health issues, child behaviors, weight loss) [18-20] is an adaptive intervention (also known as a dynamic treatment regime or adaptive treatment strategy) [21,22]. In an adaptive intervention, a sequence of intervention strategies or dosages is tailored to an individual’s needs (similar to clinical practice) as opposed to a “one size fits all” intervention approach [23]. Adaptive interventions include critical decision points (eg, which intervention to start with, when and how to measure signs of response or nonresponse), intervention components (eg, set of intervention options at each critical decision point), tailoring variables (eg, variables expected to impact the effect of the component), and decision rules (eg, links tailoring variables to the intervention components) [24]. Moreover, principles of control systems engineering can be applied to an intervention context by using decision algorithms (controllers) to regulate a dynamical system to optimize intervention outcomes [25]. For example, control systems engineering can be used to construct and estimate a dynamical model that considers how changes in an outcome (eg, weight) are related to planned and self-regulatory behaviors (eg, dietary intake, physical activity) over time. An intervention that helps each pregnant woman with overweight and obesity to control GWG on a weekly basis and adapts to her unique needs over the course of pregnancy may be a promising strategy for managing weight in pregnancy. However, we are not aware of prior research that has used this intervention approach to manage weight gain in pregnancy.

### Objectives

The primary aim of this publication is to describe the study protocol for Healthy Mom Zone, an individually tailored, adaptive intervention for managing weight in pregnant women with overweight and obesity. We will explain the conceptual framework, theoretical components, intervention dosages, and decision rules for how and when to adapt the intervention. We then describe the intensive longitudinal data collection procedures and the methods for conducting poststudy participant interviews to examine program compliance, dosage exposure, and participant responsiveness. We will also explain the plan to establish initial validation of the intervention by examining impacts of the program on GWG (ie, average weekly GWG of intervention vs control group; meeting individual GWG goals based on prepregnancy weight status), energy intake, physical activity, planned self-regulatory behaviors, and related maternal health outcomes. This work aims to use principles of control systems engineering to optimize the intervention for future application; in other words, to inform how the intervention can effectively and efficiently manage GWG in pregnant women with overweight and obesity.

## Methods

### Ethics Approval and Consent to Participate

This study has been approved by the Pennsylvania State University Institutional Review Board (Study #00000122) and Clinical Research Center (#319). All legal and data protection issues are discussed with the responsible authorities, and all participants are required to provide active informed consent.

### Overview of Healthy Mom Zone Study Design

The intervention is currently being tested in a longitudinal study design among a cohort of pregnant women with overweight and obesity randomized to either the intervention or control group from approximately 8-36 weeks gestation. Figure 1 summarizes the flow of participants through the study using the Consolidated Standards of Reporting Trials template [26]. Study measures are obtained at baseline, throughout the course of the intervention (eg, daily, weekly, and monthly), and at follow up (see Table 1). GWG is evaluated weekly and decision rules are used in 3-4 week cycles to decide when and how the intervention may be adapted for an individual. The decision to evaluate GWG in 3-4 week cycles was based on the following: (1) clinical insight and judgment (eg, prenatal care visits for most women occur in 3-4 week cycles, so we used the same cycle for our GWG evaluations), (2) reducing participant burden (eg, the 3-4 week cycle allowed women to adjust to the dosages before adaptations are made), and (3) being proactive about adjusting the intervention dosage in real-time before a woman’s weight exceeds her goal. In addition, mHealth tools are used to allow participants to self-monitor behaviors (ie, weight, physical activity, dietary intake). The study staff can review the data collected from the monitors and provide the participants with real-time feedback to facilitate compliance (eg, contact participants when the devices are not working or not being used according to the study protocol). All participants are compensated for their time spent on completing the study measures (receive gift cards and cash for pre- and postmeasures); women participating in the intervention do not have to return their Wi-Fi weight and food scales. We will use the data collected in this study and dynamical modeling from control systems engineering (system identification) to express progression of GWG over time. We will identify a customized intervention plan for each woman based on her energy intake, physical activity, planned and self-regulatory behaviors, and the extent to which she is meeting GWG goals over pregnancy. This will lead to final intervention modifications and result in an individually tailored, adaptive and optimized intervention, of which we will test efficacy in a future randomized controlled trial.

**Figure 1 figure1:**
[figure not shown]
Flow of participants through Healthy Mom Zone Intervention (still underway) as per Consolidated Standards for Reporting Trials guidelines. Participants allocated to intervention group could be assigned to various step-ups throughout the intervention time period. Step-ups will vary by individual and time-point of intervention and gestation. Incomplete cells are due to ongoing data collection.

**Table 1 table1:** Healthy Mom Zone measurement protocol. X designates when the measurement had taken place. All participants completed this measurement protocol.

Variable	Assessment	Time point						
		Pr^a^	Po^b^	D^c^	W^d^	BiW^e^	M^f^	Pp^g^
Weight and weight gain	High Precision Stand-On Adult Scale	X	X					X
	FitBit Aria Wi-Fi Smart Scale			X				X
Height	Stadiometer	X						
Serum blood	Macronutrients	X	X					
Adiposity	Air-Displacement Plethysmography (BODPOD) Body Composition	X	X					X
Healthy eating behaviors	MyFitnessPal Phone App				X			
	3-Factor Eating Questionnaire	X	X				X	
	Remote food photography		X					X
Physical activity behaviors	Actigraph (time spend in moderate-intensity activity)	X	X				X	
	Jawbone Wrist-Worn Activity Monitor	X	X	X				X
	Physical activity log (mode and min activity)							X
	Leisure-Time Exercise Questionnaire	X	X				X	
Weight attitude	Palmer attitudes toward weight in pregnancy	X	X				X	
Healthy eating and exercise motivational determinants	Attitude, subjective norm, perceived control, intention	X	X				X	
	Healthy eating and exercise beliefs	X	X		X			
Self-regulation	Self-regulation index	X	X			X		
	Self-Regulation Questionnaire (self-regulatory function)	X	X			X		
	Self-control scale	X	X				X	
Sociodemographic	Health history Questionnaire	X						
	Pregnancy complications	X			X			
Self-efficacy	Sui Healthy Eating and Physical Activity Self-Efficacy Scales	X	X				X	
	Clark Weight Efficacy Scale	X	X				X	
Sleep behaviors	Pittsburgh Sleep Quality Index	X	X				X	
	Jawbone Wrist-Worn Activity Monitor	X	X	X				X
Psychosocial	Center for Epidemiological Studies Depression Scale	X	X				X	
	State Trait Anxiety Inventory	X	X			X	X	
	Body Areas Satisfaction Scale	X	X				X	
	Perceived Stress Scale	X	X		X			
	Pregnancy Figure Rating Scale	X	X				X	
	Rothbart Adult Temperament Scale	X						
Stress	Urine cortisol collection	X	X		X			X
Metabolism	Breezing device	X	X		X			X
Fetal Growth	Standard fetal ultrasound scans						X	

^a^Pr: preintervention.

^b^Po: postintervention.

^c^D: daily.

^d^W: weekly.

^e^BiW: biweekly.

^f^M: monthly.

^g^Pp: postpartum.

### Participants and Sample Size

The target sample for this intervention is 30 pregnant women with overweight and obesity (BMI range 25-45 kg/m^2^; >40 kg/m^2^ with physician consultation); singleton pregnancy >8 weeks gestation; English-speaking; residing in or near Centre County, Pennsylvania; and with physician consent to participate. On the basis of our past research [27,28], this group compromises >85% of live births in Central Pennsylvania. Exclusion criteria are multiple gestation, diabetes at study entry, not overweight or obese, severe allergies or dietary restrictions, contraindications to prenatal physical activity [29], and not residing in area for duration of the study. The primary outcome of our study is GWG. Julious [30] effectively argues a sample size of 12 per group is adequate to assess feasibility and obtain sufficient precision of the mean and variance to perform a formal sample size and power calculation for a future larger randomized control trial with GWG as the primary outcome. With 24 participants (12 per group), we will have 80% statistical power to detect a standardized effect size (difference between 2 group means divided by SD) for GWG of 1.2 using a 2-sided test with significance level of *P*=.05. Factoring in participant dropout (conservative estimate of 25% based on our pilot work [31,32] and past research [5]), we will recruit 30 participants (15 intervention, 15 control).

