### Strengths and Limitations

There are several positive features of this study. This study has strong public health relevance and clinical significance for the future management of GWG. We have also incorporated several innovative aspects into the study, including the use of (1) novel decision rules to choose when and how to adapt the intervention, (2) mHealth tools for self-monitoring of behaviors and real-time data collection to provide feedback to the participants, and (3) a unique computerized applet to generate individualized weight gain trajectories for comparing actual weight to the Institute of Medicine guidelines. In addition, customized eating and physical activity plans developed for this study aid in reducing participant barriers to engaging in healthy behaviors during pregnancy. Moreover, the intensive longitudinal data collection protocol allows for a myriad of systems approaches in support of implementing and evaluating intensively adaptive interventions [25,56-58]. Intensive data collection enables the application of system identification and state estimation approaches from engineering that, in turn, build comprehensive dynamical models for GWG used in adaptive intervention optimization. These methods can be used to estimate and correct energy intake over time, despite some missing data.

There are also some limitations of this research. The small sample size, although adequate for examination of the primary outcome (GWG), precludes the ability to make assumptions at a population level. Moreover, the target population is a homogenous sample of women from largely rural and suburban areas in Central Pennsylvania, thus limiting the extension of the study findings to more culturally diverse and urban populations of pregnant women with overweight and obesity. We do plan to understand the application of Healthy Mom Zone to a more diverse sample of pregnant women in the future, including those who are normal weight, more culturally diverse, and reside in varied communities across the United States.

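### The dropout allowance is miscalculated: 24 evaluable women at 25% dropout need 32 recruits, and the stated 30 covers only 20% loss (minor)

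*Protocol article*

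**What the plan says.** Under Participants and Sample Size, the Protocol article gives two reasons for 12 women per group. One is a cited methodological argument that this number suffices for feasibility and for estimating the mean and variance needed to plan a later trial. The other is power: "With 24 participants (12 per group), we will have 80% statistical power to detect a standardized effect size". The effect is specified as "for GWG of 1.2 using a 2-sided test", and the error rate as "2-sided test with significance level of *P*=.05".

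The next sentence allows for loss and sets the target: "Factoring in participant dropout (conservative estimate of 25% based on our pilot work [31,32] and past research [5]), we will recruit 30 participants", 15 in each group. The section on recruitment and allocation repeats 15 and 15 with 1:1 allocation.

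The Abstract and Results report progress: 31 women recruited, 24 through follow-up, 3 in progress, 1 dropout and 3 early miscarriages. The Abstract adds that 13 of the 24 had completed the intervention.

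**The concern.** Three figures stand in consecutive sentences: 24 women needed, 25% lost, 30 recruited. They cannot all hold. Dropout is a fraction of those recruited, so the required number must be divided by the fraction retained. Multiplying it by one plus the dropout fraction gives too few.

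Both reasons for the sample size rest on 12 per group, and the power calculation has almost no slack at that number. A shortfall under the plan's own assumption therefore takes the design below its stated power. The study is also meant to inform a larger trial. The same rule carried forward at 25% dropout would recruit 30/32 = 0.9375 of the number needed, about 6% too few.

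**Working it through.** **Inputs**, all from Participants and Sample Size unless noted: 24 evaluable women, 12 per group; standardized difference d = 1.2; two-sided 0.05; dropout 25%; 30 recruits. The article does not name the test. I assume a two-sample t-test because it reproduces the stated 12 per group.

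**1. The plan's own power figure.** Power comes from the noncentral t distribution with n1 + n2 − 2 degrees of freedom and noncentrality d × √(n1·n2/(n1 + n2)). For 12 + 12 the noncentrality is 1.2 × √6 = 2.94 with 22 degrees of freedom, and power is 80.2%. Solving for 80% power gives 11.94, so 12 per group. The stated figure reproduces.

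**2. Recruits needed.**
- Correct inflation: 24/(1 − 0.25) = 32, or 16 per group.
- Source of the stated figure: 24 × 1.25 = 30, or 12 × 1.25 = 15 per group.
- Loss that 30 recruits can absorb: 1 − 24/30 = 20%.

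**3. What 30 recruits leave at 25% loss.** 30 × 0.75 = 22.5, so 22 or 23 women, 1 or 2 short of 24.

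**4. Power at those numbers, and the difference detectable with 80% power.**

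| Completers | t-test power at 1.2 SD | Difference for 80% power | Normal-approximation power at 1.2 SD |
|---|---|---|---|
| 12 + 12 | 80.2% | 1.20 SD | 83.6% |
| 12 + 11 | 78.3% | 1.23 SD | 82.0% |
| 11 + 11 | 76.3% | 1.26 SD | 80.4% |

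The normal approximation stays above 80% throughout, but it would have asked for only 11 per group. The plan's 12 matches the t-test, so the t-test column is the fair yardstick.

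**5. Reported conduct.** Losses are 1 + 3 = 4 of 31, or 12.9%. Of the 24 completers, 13 were in the intervention group, which implies 24 − 13 = 11 controls. For 13 + 11, t-test power at 1.2 SD is 79.9%. It rises if any of the 3 women in progress complete; the text available does not give their group.

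**The case against.** The best answer is that the slip did no harm. The article calls 25% conservative, and the reported loss of 12.9% is about half of that. The required 24 completers were reached, and up to 27 are possible. This stands, and it limits the weight of the point. It does not make the planning sentence right: 24 was reached because loss was lower than assumed and one extra woman was recruited.

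The planned linear mixed-effects models can also use partial weight data from women who leave, and weight is measured daily at home. Power based on completers alone is therefore the pessimistic end. That is fair, but the documents do not allow the gain to be computed, and the article's own power statement counts 12 women per group.

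Power is also not the only basis for the size. The feasibility and precision argument stands beside it, and going from 12 to 11 per group raises the standard error of a group mean by only about 4% (√(12/11) = 1.044). This too stands.

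A reader might infer something stronger: that the trial fails to deliver its 80% power, or that the Strengths and Limitations sentence is wrong ("The small sample size, although adequate for examination of the primary outcome (GWG"). The documents support neither. The shortfall exists only under the 25% assumption, and the reported numbers give about 80%. The word about adequacy sits in a sentence that admits the small sample as a limitation, and the size also has its precision rationale. Rewording it would be a preference, not a correction of arithmetic.

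**Conclusion.** The sentence is wrong as written, and the matter is minor. At 25% dropout, 24 evaluable women require 32 recruits; 30 is enough only for a loss of 20% or less. Under the plan's own assumption the design has about 76% to 78% power for 1.2 SD, which is 2 to 4 percentage points below the stated 80%.

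The recruitment arithmetic needs no assumption beyond the article's figures. The power figures rest on a two-sample t-test at two-sided 0.05 in completers only, with the 22 or 23 women split as evenly as possible. Nothing here shows that the trial as conducted is short of women, and no analysis or conclusion changes.

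**What to change.** Correct one sentence in Participants and Sample Size, in either of two ways:

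- Keep the sourced 25% and state that 30 recruits would leave 22 to 23 evaluable women, with about 76% to 78% power for a 1.2 SD difference (80% power for about 1.23 to 1.26 SD), and that 32 recruits would have been needed for 24.
- State that 30 recruits yield 24 evaluable women only if dropout is at most 20%. Word this as a condition and do not present it as a new dropout estimate, since the article attributes 25% to its sources and gives nothing in support of 20%.

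No extra enrolment is needed, and the wording in Strengths and Limitations can stay. The cost is one edited sentence and, with the first option, a slightly less favourable power figure. Any calculation for the later trial should divide by the fraction expected to be retained.
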